### Data management

All researchers, including acupuncturists, outcome assessors, and statisticians, have received training in data management. The data will be entered into the CRF system, which was established before the recruitment process. The clinical research associates will be responsible for ensuring the accuracy of the data. Online monitoring will be used during the trial to ensure that the data is collected completely and accurately. The “check” function in the CRF system will assist with dynamic data management. Once the study is complete, the data management team will implement data lockup, and researchers will be unable to modify the data. All research documents, including paper files and electronic documents, will be kept for at least 5 years after publication. If reviewers or readers have any questions regarding the published data, they can contact the corresponding author for access to the original data. To ensure confidentiality, private patient information, such as names, telephone numbers, and identification numbers, will remain anonymous.

### Quality control

The trial protocol has been thoroughly reviewed and revised by experts in acupuncture, methodology, and statistics. Standard operating procedures have been established to conduct the intervention, complete the CRF, assess the outcomes, and manage data. The relevant staff has been trained accordingly to ensure adherence to these procedures. An inspection plan will be designed to ensure quality control. For patients, quality control can be carried out by randomly selecting several individuals and confirming their authenticity through phone calls. Patients and researchers will be spot-checked to ensure that their informed consent process is ethical. The key focus during the intervention will be to standardize the manipulation process to investigate whether the implementation process of acupuncture is carried out by this clinical study. Specifically, it includes whether the intervention implementer has received training for this study, the accuracy of the acupoint selection, the standardization of disinfection, the method and scale of needle insertion, and the standardization of manipulation. We will conduct face-to-face interviews with the intervention implementers, monitor the actual research process, or monitor the implementation process through simulation.

### Sample size

The purpose of this study was to evaluate the study’s feasibility and support the development of a future definitive RCT. Utilizing the upper confidence limit method, we determined that a pilot sample size of between 20 to 40 individuals can serve as a benchmark (34). Based on the consensus of the methodologists, statisticians, and acupuncturists, we decided that a sample size of 30 in each group (25) and a 20% estimated dropout rate were sufficient; thus, the total of 114 patients would be considerable (38 in each group).

### Statistical analysis

Intention-to-treat (ITT) analysis encompassing all randomized patients will be conducted for all efficacy analyses. Additionally, a per-protocol (PP) analysis focusing on the primary outcome will be performed as a sensitive analysis, excluding patients who did not complete the acupuncture treatment. Missing outcome data will be complemented using multiple imputations with the package “Mice” from the R software (www.r-project.org).

Categorical variables will be reported by number and percentage, whereas continuous variables will be represented by mean and standard deviation (SD) (or median and interquartile range, IQR). The retention rate and treatment adherence will be reported in descriptive statistics.

For the primary outcome, CPR will be compared by the proportions of included patients with clinical pregnancy. To determine the independent factors, logistic regression will be used to identify baseline variables that are associated with outcomes. The retention rate and rates of biochemical pregnancy, ongoing pregnancy, blinding assessments, and adverse events will undergo statistical analysis using chi-squared tests or Fisher’s exact test. Other outcomes will be evaluated using one-way variance (ANOVA) models or Kruskal–Wallis analysis. The score of SAS, SDS, FertiQol, and PSQI, respectively, will be assessed at baseline and after treatment among groups on hCG trigger day. Statistical significance will be determined at *P <*0.05. Pairwise comparisons will be performed between the EA + IVF group and the pEA + IVF group and between the EA + IVF group and the IVF group in a *post hoc* analysis.

A predetermined subgroup analysis will be performed to determine whether the baseline characteristics (female age, ovarian stimulation protocol, etc.) affect the CPR to EA. The data was analyzed using SPSS version 27.0 (IBM, Armonk, NY, USA). As this is a pilot study, our results were considered exploratory.

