### Intervention

Patients in the three groups will receive GnRH-a or GnRH-A protocol according to the previous study (21, 22). Egg retrieval, fertilization, and embryo transfer were determined by their fertility specialists. During the study period, the patients’ medications, including dose and types, should be recorded in detail.

Following the randomization, the patients who were randomized into the EA + IVF group and the pEA + IVF group will receive EA treatment during the ovarian stimulation phase at three times per week (every other day) until trigger day with a minimum five session. Each session will continue for 30 min. Licensed acupuncturists possessing a minimum of 1 to 3 years of clinical experience will undergo training in a standardized operating procedure. This training aims to impart a comprehensive understanding of the precise locations of acupoints and non-acupoints. Additionally, they will acquire proficiency in needle manipulation and the operation of electro-devices. Only acupuncturists who have completed this training will be authorized to perform acupuncture treatments.

The disposable needles (Hwato, Suzhou, Jiangsu, China) and the SDZ-V EA apparatus (Suzhou Medical Appliance) have the same appearance. The needle device used for blinding is comprised of a sticky plastic plate with a guide tube. The needles and blunt-tip needles will be administered through the guide tube and the hole of the plastic plate.

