#### IVF control group

Patients in the IVF control group will not receive any EA treatment during the ovarian stimulation phase. After the end of the follow-up period, the participants will receive compensation after the follow-up period ends.

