PSQI	PSQI contains 19 items, and its measurement is determined by calculating the sum of the scores of each item	Baseline and on trigger day
Adverse events		
	Including nausea during the ovarian stimulation, hematoma around the site of needling, infection around the site of needling, dizziness after acupuncture, and other discomforts after acupuncture	After each treatment

a The rates of pregnancy outcomes are defined as the number of pregnancy outcome cycle per ovarian stimulation cycle.

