#### Secondary outcomes

The secondary outcomes include embryology data, other pregnancy outcomes, and the scale and questionnaire measurement. The schedule of measurements and visits for each outcome are shown in **Table 4**. We will also observe the patient retention rate and treatment adherence. Retention rate is defined as the percentage of patients enrolled at baseline and who completed all follow-up measurements. Treatment adherence is assessed using attendance at the treatment sessions. Successful pilot targets are defined as the recruitment of 114 participants over 4 months, an 80% retention rate (25), and at least four treatment sessions attended.

Embryology data include total ova retrieved and total high-quality embryos. The high-quality embryos will be graded according to the guidelines (26, 27) by embryologists. Cleavage-stage embryos and blastocyst-stage embryos will be recorded separately.

The follow-up of pregnancy outcomes will be observed around 14 days and 12 weeks after embryo transfer. Besides CPR, the biochemical pregnancy rate (BPR), embryo implantation rate, and early miscarriage rate will also be observed, respectively. BPR is defined as the level of human chorionic gonadotropin (hCG) >5 mIU/mL (28). The fertilization rate is defined as the number of 2PN embryos divided by the number of inseminated oocytes. The early miscarriage rate is defined as the fetal growth stops or the absence of heart activity in the gestational sac within the first 12 weeks of pregnancy.

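### The per-protocol rule can exclude women only from the two acupuncture arms, so a per-protocol EA versus IVF control comparison is no longer randomised

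*Protocol article*

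**What the plan says.** The Statistical analysis section sets the main analysis first: "Intention-to-treat (ITT) analysis encompassing all randomized patients will be conducted for all efficacy analyses". It then adds a second one: "a per-protocol (PP) analysis focusing on the primary outcome will be performed as a sensitive analysis", and gives a single exclusion for it: "excluding patients who did not complete the acupuncture treatment". No matching criterion is stated for the control arm. The same section plans pairwise comparisons of EA with pEA and of EA with IVF control, and does not say that the per-protocol analysis leaves out the second.

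The section on the control arm reads: "Patients in the IVF control group will not receive any EA treatment during the ovarian stimulation phase".

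Three further statements bear on who counts as a completer and how she is counted:

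- Intervention: sessions run "at three times per week (every other day) until trigger day with a minimum five session".
- Secondary outcomes: the pilot target for adherence is "at least four treatment sessions attended".
- Table 4, footnote a (Outcome measurement): "The rates of pregnancy outcomes are defined as the number of pregnancy outcome cycle per ovarian stimulation cycle".

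**The concern.** A per-protocol rule that can act in two arms and not in the third compares a selected group with an unselected one. Some women in the control arm would not have completed acupuncture had they been assigned to it. They stay in the analysis, while their counterparts in EA and pEA are dropped.

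The selection need not be neutral. Sessions are tied to the stimulation phase, so whether a woman completes depends partly on how her cycle goes after randomisation, and that may be related to whether she conceives. A sensitivity analysis is there to show whether the main result is robust. One whose exclusions are specific to the arm and possibly linked to the outcome cannot do that for EA versus IVF control. The pilot is meant to support a later definitive trial, so a misleading per-protocol contrast could colour that decision.

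**Working it through.** **Does the rule reach the control arm?** No. The only exclusion is failure to complete acupuncture, and control women are assigned none. All control women stay in, about 38 under the Sample size section. That figure reproduces: 30 / (1 − 0.20) = 37.5, rounded up to 38, and 3 × 38 = 114.

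**Can completion depend on the cycle?** This turns on what completion means. If it means the five-session minimum, and sessions start on day 1 and run every other day, the fifth falls on day 1 + 2 × 4 = 9 at the earliest. A cycle stopped or triggered before then cannot reach five, however well the woman attends. With pregnancy counted per stimulation cycle, a cycle stopped without a transfer is a non-pregnancy. It would be dropped from EA and pEA and kept in control.

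**Size of the bias under no treatment effect.** Let c be the clinical pregnancy rate (CPR) in completers, r the rate in non-completers and q the share of non-completers, the same in all arms.

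- EA, per-protocol: c
- IVF control, nobody excluded: p = (1 − q)c + qr
- Bias, EA minus IVF: c − p = q(c − r), which equals q(p − r)/(1 − q)

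The article gives no value for c, r or q, so these are assumptions. The 20% equals the dropout rate in the Sample size section, but that is a figure for all groups and not a rate of acupuncture non-completion. It serves here only as an illustration.

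| c | q | r | CPR in IVF control | Bias (points) |
|---|---|---|---|---|
| 45% | 20% | 10% | 0.8 × 45 + 0.2 × 10 = 38% | +7.0 |
| 45% | 10% | 20% | 0.9 × 45 + 0.1 × 20 = 42.5% | +2.5 |
| 45% | 30% | 0% | 0.7 × 45 + 0.3 × 0 = 31.5% | +13.5 |
| 45% | 20% | 45% | 45% | 0 |
| 45% | 20% | 55% | 0.8 × 45 + 0.2 × 55 = 47% | −2.0 |

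The sign is that of c − r. The first three rows are positive because they assume that non-completers do worse; the last two show what happens without that assumption.

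**Effect on the test.** These are exact enumerations of an uncorrected two-sided chi-squared test at 0.05. Per-protocol has 30 EA women (0.8 × 38 = 30.4) against 38 controls; intention-to-treat has 38 against 38.

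- True rates 45% and 38%, as in the first row: rejection in 9.5% of trials, against 4.9% for intention-to-treat at 38% in both arms. The standard error of the per-protocol difference is √(0.45 × 0.55/30 + 0.38 × 0.62/38) ≈ 0.12, or 12 points.
- Extreme case in which no non-completer conceives, q = 20%, true rate p of 30%, 40% or 50% in every arm: rejection in 11.9%, 13.2% and 17.2%, against about 5% for intention-to-treat.

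**The case against.** A reader might infer that the per-protocol analysis is bound to show a benefit of acupuncture over IVF control even if there is none. The documents do not support that. They give no pregnancy rate by completion status, and women may stop acupuncture for reasons unrelated to ovarian response. Women triggered before day 9 would also fail a five-session rule, and nothing in the article says that they do worse. Even in the 7-point illustration, more than nine trials in ten would show no significant difference.

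A reader might also take completion to mean five sessions. The article does not say so. Every session up to the woman's own trigger day is an equally available reading, and under it a short stimulation is not in itself non-completion.

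Other points limit the weight of the concern. The per-protocol analysis is secondary to intention-to-treat, and results are labelled exploratory. The pilot success targets are recruitment, retention and attendance, not pregnancy. The article does not explicitly tie the per-protocol analysis to EA versus IVF control, and a fuller definition of the set may stand in a document not shown.

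All of this stands as a limit on direction, size and consequence. It does not remove the flaw. The exclusion rule is stated, not left open, and it has no counterpart in control. The comparison with control is planned and is not exempted. The loss of the randomised comparison does not depend on the sign of the bias.

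**Conclusion.** The concern holds in a limited form. As written, the rule breaks the randomised comparison of EA with IVF control in the per-protocol analysis of the primary outcome. Bias towards acupuncture is the likelier direction under a five-session reading, because cycles stopped early count as non-pregnancies and would leave only the acupuncture arms. That direction is an inference and not something the documents establish. With 45% CPR in completers the bias runs from +2.5 to +13.5 points for 10% to 30% excluded at a CPR of 20% down to 0%. It is zero at equal rates and negative if non-completers do better.

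The EA versus pEA contrast is less exposed, because the same rule applies to both arms; it is affected if the extent or the kind of non-completion differs between them. The main intention-to-treat result is untouched. The problem should be corrected before analysis, but it is confined to a sensitivity analysis.

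**What to change.** 1. Restrict the per-protocol analysis to EA versus pEA, and use intention-to-treat only for EA versus IVF control.
2. Define completion for this analysis set before the data are seen, as attendance at the sessions scheduled up to the woman's own trigger day. State how a cycle stopped before trigger is classified, so that a short stimulation is not in itself counted as non-completion.
3. Reconcile that definition with the five-session minimum under Intervention and the four-session target under Secondary outcomes. The article ties per-protocol completion to neither.

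Filtering all three arms on reaching trigger day is a weaker alternative. It treats the arms alike, but still conditions on an event after randomisation that EA, which is intended to improve ovarian response, might affect.

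The cost is a change of analysis wording and the loss of the per-protocol estimate for EA versus IVF control. Treatment, data collection and sample size do not change.

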### Randomization and allocation concealment

Randomization will be conducted after the patients agree to consent to undertaking acupuncture treatments. Patients will be randomized according to the randomized number table generated by SPSS (version 27.0, IBM, Armonk, NY, USA) after completing the baseline assessments. Patients will be randomized into three groups: electro-acupuncture with IVF treatment (EA+ IVF group), placebo electro-acupuncture with IVF treatment (pEA + IVF group), and only IVF control (IVF group) in a 1:1:1 ratio using stratified block randomization (block = 3 or 6, randomly). An independent statistician with no clinical role in this study will comply with the randomization sequence. Allocation concealment was ensured by using a telephone by an independent third party to ensure objectivity and minimize the risk of bias.

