#### Primary outcome

In this feasibility and prior study, the primary outcome is the CPR, defined as the rate of achieving clinical pregnancy from the first fresh/frozen embryo transfer cycle with an ultrasound-confirmed gestational sac in the uterine cavity (24) as measured 28 days after embryo transfer.

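### Randomisation is stratified, but the stated comparison of clinical pregnancy rates makes no use of the strata, and the only model tied to that outcome is not used to estimate the treatment effect

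*Protocol article*

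**What the plan says.** Under Randomization and allocation concealment, women are allocated 1:1:1 to three arms "using stratified block randomization (block = 3 or 6, randomly"). The stratification factors are not named.

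Under Primary outcome, "the primary outcome is the CPR, defined as the rate of achieving clinical pregnancy from the first fresh/frozen embryo transfer cycle". Under Statistical analysis, "CPR will be compared by the proportions of included patients with clinical pregnancy". No test, effect measure or adjustment is attached to that sentence. The next sentence introduces the only model tied to CPR: "logistic regression will be used to identify baseline variables that are associated with outcomes". It mentions neither arm nor strata.

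The methods for the remaining outcomes have no strata either. Retention, biochemical pregnancy and other rates "will undergo statistical analysis using chi-squared tests or Fisher’s exact test", and "Other outcomes will be evaluated using one-way variance (ANOVA) models or Kruskal–Wallis analysis". The two comparisons of EA with the other arms are named, but as a post hoc step. Female age and stimulation protocol appear only as subgroup variables. A threshold of P<0.05 is set, and the section closes by calling the results exploratory.

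**The concern.** Stratified blocks force the arms to be balanced on the stratification factors. Where those factors predict pregnancy, part of the outcome variation cannot contribute to a chance difference between arms. An analysis that ignores the strata still counts that part as error. With balanced strata the estimated difference hardly moves, but its standard error is overstated, the P-value is too large and any interval is too wide. The design effort is then partly wasted.

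The natural remedy is a model or stratified estimate containing arm and strata. The article does name a logistic model for CPR, but gives it the task of finding prognostic variables. The Sample size section says the pilot is meant to support a future definitive trial. For that, the useful result is the EA effect on CPR with an honest measure of its uncertainty.

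**Working it through.** **The plan's own figure.** Sample size gives 30 per arm and 20% dropout: 30/(1 − 0.20) = 37.5, rounded up to 38, and 3 × 38 = 114. This reproduces, and 38 per arm is used below.

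**Size of the overstatement.** The article gives neither the strata nor any CPR by stratum, so the stratum rates are assumptions. Take two equal strata with rates p1 and p2, mean p, n = 38 per arm, and no treatment effect.

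- Variance used by the unstratified comparison: 2p(1 − p)/n
- Variance of the difference under stratified allocation: [p1(1 − p1) + p2(1 − p2)]/n
- Variance ratio: [p1(1 − p1) + p2(1 − p2)] / [2p(1 − p)]; overstatement of the standard error: 1/√ratio

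For 50% and 25%: (0.2500 + 0.1875)/(2 × 0.375 × 0.625) = 0.4375/0.46875 = 0.933, and 1/√0.933 = 1.035. The 95% half-width 1.96 × √(variance) is 1.96 × √(0.46875/38) = 21.8 points unstratified, against 1.96 × √(0.4375/38) = 21.0 points.

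For 55% and 15%: (0.2475 + 0.1275)/(2 × 0.35 × 0.65) = 0.375/0.455 = 0.824, and 1/√0.824 = 1.10. The half-widths are 1.96 × √(0.455/38) = 21.4 points and 1.96 × √(0.375/38) = 19.5 points.

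For a weak split, 45% and 35%: (0.2475 + 0.2275)/(2 × 0.40 × 0.60) = 0.475/0.48 = 0.990, and 1/√0.990 = 1.005. That is no practical loss.

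**Effect on the test.** This was simulated with 6,000 trials per scenario: 114 women, three arms, permuted blocks of 3 or 6 within four assumed strata of equal expected size, EA versus placebo EA. An uncorrected chi-squared test was compared with the Cochran-Mantel-Haenszel (CMH) test at two-sided 0.05. Two-sided is an assumption, because the article does not say.

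| Assumed stratum CPRs | Type I error, unstratified / CMH | Power at assumed odds ratio 3, unstratified / CMH |
|---|---|---|
| Weak (45, 42, 38, 35%) | 0.051 / 0.049 | 0.66 / 0.65 |
| Moderate (60, 50, 30, 20%) | 0.040 / 0.047 | 0.57 / 0.60 |
| Strong (75, 55, 25, 10%) | 0.026 / 0.054 | 0.39 / 0.51 |

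The direction agrees with the variance calculation. The unstratified test is conservative where the strata matter and equivalent where they do not. The power loss is about 3 points for moderate and about 13 points for strong strata.

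**The case against.** The strongest reply is that this is a condensed article. The CPR sentence does not say unadjusted, and a Mantel-Haenszel analysis also compares proportions, so the neglect of the strata is partly read from silence. That is fair as a caution, and it limits the point to what is stated. It does not remove the point. The article fixes a stratified design, describes the analysis of each type of outcome without the strata, and gives its logistic model another job.

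Several stronger readings are tempting, and the document does not support them.

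- *No treatment effect or confidence interval is planned.* None is stated, but a full analysis plan may contain both.
- *The predictor model is improper.* No selection procedure is given and arm is not said to be excluded. It can stand as a separate secondary analysis.
- *The contrasts of interest are unplanned.* Both are named in advance. In a three-arm trial, post hoc commonly means the pairwise step after an overall test.
- *The results could be falsely positive.* The calculations show the opposite direction.
- *The low power shows the harm.* At 38 per arm and CPR 40% the half-width is 1.96 × √(2 × 0.4 × 0.6/38) = 22 points, and power for 40% versus 55% is about 26%. Those figures reflect the sample size, which stratifying would hardly change. The trial is also sized for feasibility and its results are labelled exploratory. A threshold such as 24/38 against 15/38 depends on the test: P = 0.039 by uncorrected chi-squared, but 0.066 by Fisher's exact test.

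**Conclusion.** The point holds in a limited form. As stated, the CPR comparison does not use the strata that the randomisation uses, and the only model tied to CPR is not used to estimate the EA effect. If the strata predict pregnancy, the consequence is a loss of efficiency in the conservative direction. The standard error is about 3.5% to 10% too large under the assumed two-stratum rates of 50/25% to 55/15%, and the loss is negligible for weak strata. The larger power loss of about 13 points needs assumed stratum rates running from 10% to 75%.

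Because the factors are unnamed, the document cannot show where in this range the trial lies. This does not threaten validity. It is worth correcting because it costs almost nothing and gives the definitive trial a better-founded estimate.

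**What to change.** In the analysis section or the analysis plan, before the data are analysed:

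1. Name the stratification factors actually used in the randomisation list.
2. Make EA versus placebo EA and EA versus IVF alone the planned contrasts on CPR. Estimate each with a 95% confidence interval from an analysis containing arm and those factors: a Mantel-Haenszel risk difference, or logistic regression with marginal risk differences. If some strata are sparse, use Mantel-Haenszel or a penalised fit.
3. Keep the logistic search for associated baseline variables, described as a separate exploratory analysis.
4. State that results against "Statistical significance will be determined at" P<0.05 are read in line with the exploratory status already declared.

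The cost is wording and a few lines of analysis. Sample size, data collection and trial conduct do not change.

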#### Blinding assessment

To test whether blinding is successful, patients in the EA + IVF group and pEA + IVF group will be asked to guess which kind of acupuncture they received at hCG trigger day after finishing the acupuncture treatment.

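### A chi-squared or Fisher test at P<0.05 on 30 to 38 women per arm cannot establish that blinding worked; arm-specific estimates with intervals are needed

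*Protocol article*

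**What the plan says.** The Blinding assessment section of the protocol article gives the purpose: "To test whether blinding is successful, patients in the EA + IVF group and pEA + IVF group will be asked to guess" which treatment they had, on trigger day. The IVF-only arm is not asked.

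The Statistical analysis section gives the method: "blinding assessments, and adverse events will undergo statistical analysis using chi-squared tests" or Fisher's exact test. The same section sets the threshold ("Statistical significance will be determined at" P<0.05), has categorical variables reported as numbers and percentages, and calls the results exploratory. The article attaches no interval, blinding index or acceptable limit to the guesses.

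The Sample size section fixes the numbers: "a sample size of 30 in each group (25) and a 20% estimated dropout rate were sufficient", hence "the total of 114 patients would be considerable (38 in each group"). It says that the study is meant to "support the development of a future definitive RCT".

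**The concern.** The purpose and the method do not match. The null hypothesis of the test is that guesses do not differ between EA and pEA. A small P value is evidence against blinding. A large one is compatible with good blinding and also with too few women to see a failure, and at this size the second explanation is a live one.

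A single P value also combines the two arms. The sham differs from EA in ways a woman might notice: no skin penetration, De qi avoided, and 0.1 mA against a range of 0.1 to 5 mA. Correct guessing could therefore be concentrated in one arm.

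Whether this sham is credible is something the definitive trial will want to learn from the pilot, so the uncertainty about it should be visible.

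**Working it through.** **Inputs.** From the Sample size section: 30 evaluable per arm, 20% dropout, 38 randomised per arm. From Statistical analysis: chi-squared or Fisher, P<0.05. Assumed: a two-sided test, every woman giving one of two answers, and the guess rates, which are shown as a range because the documents give none.

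**The plan's own figure.** 30 / (1 − 0.20) = 37.5, rounded up to 38; 3 × 38 = 114. It reproduces.

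**Power by normal approximation, 60% v 40%, n = 38.** The mean proportion is 0.5.
- z = [0.20 × √38 − 1.96 × √(2 × 0.5 × 0.5)] / √(0.6 × 0.4 + 0.4 × 0.6) = (1.233 − 1.386) / 0.693 = −0.22, so power is about 41%.
- With √30 in place of √38: (1.095 − 1.386) / 0.693 = −0.42, about 34%.

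**Exact power**, from enumerating every 2×2 table (uncorrected chi-squared / Fisher):

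| Guess real EA, EA v pEA | Gap (points) | n = 38 per arm | n = 30 per arm |
|---|---|---|---|
| 55% v 45% | 10 | 14% / 10% | 12% / 8% |
| 60% v 40% | 20 | 42% / 33% | 35% / 26% |
| 70% v 50% | 20 | 43% / 34% | 35% / 26% |
| 80% v 60% | 20 | 49% / 40% | 39% / 30% |
| 65% v 35% | 30 | 76% / 68% | 66% / 56% |
| 70% v 30% | 40 | 95% / 92% | 90% / 84% |

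At 60% v 40% the test therefore misses the gap 58% or 67% of the time (n = 38) and 65% or 74% (n = 30). With guesses symmetric about 50%, power passes one half at a gap of about 23 to 25 points (n = 38) or 25 to 29 points (n = 30). For 80% power at a 20-point gap, 97 women per arm would be needed.

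**A single result.** Suppose 23 of 38 EA and 15 of 38 pEA women guess real EA. Then P = 0.066 (chi-squared) or 0.108 (Fisher), which is not significant. The gap is 8/38 = 21 points, with standard error √(2 × 0.605 × 0.395 / 38) = 0.112 and 95% CI −1 to 43 points. That interval covers both intact blinding and marked failure.

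**Why one P value hides the arms.** With two answers, the Bang index in an arm is 2 × (share guessing correctly) − 1. Write a and b for the shares guessing real EA in the EA and pEA arms. The indices are 2a − 1 and 1 − 2b, and their sum is 2(a − b). The test sees only that sum. At 60% v 40% the indices are 0.20 and 0.20; at 80% v 60% they are 0.60 and −0.20. The patterns are quite different, but the gap is 20 points in both.

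**Precision of the index.** The half-width near an index of zero is 1.96 × 2 × √(0.25/n): 0.32 at n = 38 and 0.36 at n = 30.

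**The case against.** - **No rule equates P>0.05 with success.** A reader might infer one from the stated purpose of the guess, and from the Discussion's statement that the demand for blinding of patients is met. The article sets no such rule and calls its results exploratory. This stands: the fault is that the test cannot answer the question, not that a false claim of success is planned.
- **Marked unblinding would usually be found.** This also stands. It would be wrong to say that the test usually misses real unblinding in general; that holds only below the gaps given above. The contrast between EA and sham could well produce a larger gap.
- **Counts and percentages will be reported.** A reader could see which arm guessed correctly and work out an index. This weakens the complaint about a single P value, but counts alone state no uncertainty.
- **The index detects no better.** True. At 60% v 40% and n = 38 each arm's index is 0.20 with standard error 2 × √(0.24/38) = 0.159. It would exclude zero about 24% of the time (0.20/0.159 = 1.26; 1.26 − 1.96 = −0.70), against 42% for chi-squared. The gain is honest uncertainty, not sensitivity.
- **Blinding is not among the pilot's success targets**, which are recruitment, retention and attendance. So the documents do not support the inference that the larger trial would inherit a failed sham.
- **An unseen analysis plan could add an index.** Possibly, but the article already names a method for a stated purpose, and that method does not serve it.

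**Conclusion.** The point holds in a limited form and is minor. The named test cannot establish successful blinding with 30 to 38 women per arm. A 20-point gap at 60% v 40% would be missed more often than found (58% to 67% at 38 per arm, 65% to 74% at 30), while a 40-point gap would be found 84% to 95% of the time across the two sizes and two tests. These figures rest on the assumed guess rates, a two-sided 0.05 level and a two-option answer. The harm is bounded: this is a secondary check in an exploratory pilot, the raw counts will be available, and no decision is tied to the result.

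**What to change.** In Statistical analysis, take the blinding assessment out of the list of outcomes judged only by chi-squared or Fisher, or keep the test and add to it. Report the guess proportions for EA and for pEA separately, each with a Bang blinding index and 95% confidence interval. State that P>0.05 will not be taken as evidence of successful blinding.

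The cost is about one sentence of text. It uses the data already being collected. The question put to women should stay as it is, because recruitment is under way (Trial status) and the article does not state the current response options. The one drawback is that the intervals will be wide, so the pilot may have to report blinding as inconclusive.
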